3. Overall, breast cancer-specific and recurrence-free survival at 2, 5 and 10 years. For overall survival, censuring is at death or at date for latest follow-up. For breast cancer-specific survival, censuring is at breast cancer-specific death or at date of last follow-up. For recurrence-free survival, censuring is at first local, regional or distant recurrence or at death or date of last follow-up. Contralateral invasive or in situ breast cancer or non-breast secondary malignancies are not counted as an event, in accordance with STEEP criteria^32^.
4. Health-related quality of life including fatigue, assessed by the EORTC QLQ-C30 and BR23 questionnaires (baseline, pre-surgery, 1- and 2-year follow-up)
5. Self-reported physical activity (Modified Godin Leisure Time Physical activity questionnaire) at baseline, pre-surgery, and 1- and 2-year follow-up, facilitating subsequent adjustment for any cross-contamination in the control group
6. Toxicity-related outcomes:
   1. Chemotherapy completion rates, i.e. the proportion of participants receiving the planned number of treatments at full dosage regarding neoadjuvant chemotherapy (measured pre-surgery).
   2. Number of unplanned hospital admissions during neoadjuvant chemotherapy.
   3. Objective cognitive dysfunction measured by an online neuropsychological test (Amsterdam Cognition Scan)^33^ (baseline and 1-year follow-up).
   4. Cardiac toxicity (defined as either left ventricular ejection fraction (LVEF) decline >15% or LVEF decline below an absolute value of 50% or clinical heart failure), to be measured by echocardiogram at baseline and after 3 months of NACT in the HER2-positive subgroup
   5. Sick leave (patient-reported percentage of sick leave as a single measurement pre-surgery and at 1- and 2-year follow-up)
7. Device-measured physical activity level and resting heart rate assessed through the Fitbit activity tracker (baseline to 1-year follow-up).
8. Muscle strength assessed through the handgrip strength test and hypothetical 1-RM maximal leg muscle strength tests (baseline and pre-surgery).
9. Cardiorespiratory fitness assessed by the Ekblom-Bak submaximal cycle test (baseline and pre-surgery).

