#### Secondary endpoints

1. *Residual Cancer Burden (RCB)*

Residual Cancer Burden (RCB) is measured as four ordered categories (RCB-0 which corresponds to pCR, RCB-I, RCB-II, and RC-III) at histopathological assessment of the surgical specimen. An ordinal regression model, adjusting for biological tumour type (stratification factor in the randomization), will be used to analyse differences between the treatment arms. If the proportional odds assumption of the model is violated, a nominal regression model or a generalized logistic model will be used instead if appropriate.

1. *Objective tumour response*

Response Evaluation Criteria in Solid Tumours (RECIST) will be applied in order to assess change in radiological tumour size (%) from baseline to pre-surgery imaging. RECIST criteria classify response into four ordinal outcome categories: complete response, partial response, stable disease and progressive disease (see page 18)^31^. An ordinal regression model, adjusting for biological tumour type (stratification factor in the randomization), will be used to analyse differences between the treatment arms. If the proportional odds assumption of the model is violated, a nominal regression model or a generalized logistic model will be used instead if appropriate. Tumour size at histopathological assessment of the surgical specimen may be included in comparative analyses. Mean difference in reduction of tumour size between treatment arms will be analysed with an ANOVA, including biological subtype as a factor in the model.

1. *Survival outcomes*

All-cause, breast cancer-specific and recurrence-free survival will be analysed at 2, 5 and 10 years. Contralateral breast cancer is not regarded an event. Difference in time-to-event outcomes between treatment arms will be compared. The mortality outcomes are defined as time from date of randomisation to death (from any cause or breast cancer as underlying cause, respectively) or censoring at end of follow-up. For recurrence-free survival, the outcome is measured as time from date of randomisation to breast cancer relapse or censoring at end of follow-up. Survival estimates after 2, 5 and 10 years of follow-up will be compared using Kaplan-Meier estimates. Furthermore, a Cox regression model, adjusting for biological subtype will also be used.

1. *Health-related quality of life*

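### Recurrence-free survival is defined in two ways: the endpoint section ends it at recurrence or death, the analysis section counts relapse only

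*Protocol*

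**What the plan says.** Survival is the third secondary endpoint, and the protocol defines it in two places.

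**Outcomes, Variables and measures, item 3**
- Recurrence-free survival: "For recurrence-free survival, censuring is at first local, regional or distant recurrence or at death or date of last follow-up".
- Overall survival: "For overall survival, censuring is at death or at date for latest follow-up".
- Breast cancer-specific survival: "For breast cancer-specific survival, censuring is at breast cancer-specific death or at date of last follow-up".
- Exclusions: "Contralateral invasive or in situ breast cancer or non-breast secondary malignancies are not counted as an event, in accordance with STEEP criteria".

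**Statistical analysis plan, Secondary endpoints, Survival outcomes**
- Mortality outcomes: "The mortality outcomes are defined as time from date of randomisation to death". This covers both all-cause and breast cancer deaths.
- Recurrence-free survival: "For recurrence-free survival, the outcome is measured as time from date of randomisation to breast cancer relapse or censoring at end of follow-up".
- Method for the curves: "Survival estimates after 2, 5 and 10 years of follow-up will be compared using Kaplan-Meier estimates".
- Method for the regression analysis: "Furthermore, a Cox regression model, adjusting for biological subtype will also be used".

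Three other places bear on the point. The End of trial section ends a participant's trial at two years after surgery, or earlier on death, withdrawal or loss to follow-up. The Synopsis takes survival and recurrence at 5 and 10 years from national registers. The Additional measures section says that the trial is not powered for survival and recurrence.

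**The concern.** The two sections disagree on whether a patient who dies without a recorded relapse has had a recurrence-free survival event. That choice changes the number of events, the height of the curve and the meaning of the hazard ratio. Two analysts, each following one section faithfully, would report different results under the same endpoint name. If the question is settled only after survival data are available, the choice can be made with the results in view.

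The loose use of *censuring* adds to the problem. Taken literally, the endpoint section censors every patient and gives none of the three survival endpoints an event.

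Breast cancer-specific survival has a smaller gap of the same kind: neither section says when a patient who dies of another cause leaves the risk set.

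**Working it through.** **1. Does the plan give a figure to reproduce?** Not for this endpoint: it states no event number, rate, hazard ratio or power for recurrence-free survival. Its only sample-size figure is for pathological complete response (30% against 40%, two-sided 5%, power 80%), and it reproduces:

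n per arm = [1.96 × √(2 × 0.35 × 0.65) + 0.8416 × √(0.30 × 0.70 + 0.40 × 0.60)]² / 0.10² = 356, so 712 in total.

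With 10% dropout, 712 / 0.9 = 791, or 792 for equal arms, against 790 stated. None of this depends on the survival definitions.

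**2. The two definitions side by side**

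| | Endpoint section | Analysis section |
|---|---|---|
| Recurrence | ends the time | event |
| Death without recurrence | ends the time | not mentioned |
| Alive without recurrence | last follow-up | end of follow-up |

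Is death an event in the endpoint section? It says *censuring*, but it uses the same word for death in overall survival and for breast cancer death in breast cancer-specific survival, where these can only be events. Its listed exclusions are contralateral breast cancer and non-breast malignancies; death is not among them. The consistent reading is that recurrence and death are both events.

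The analysis section names death for the mortality outcomes and, in the next sentence, leaves it out for recurrence-free survival.

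**3. Direction.** If any death occurs without relapse, leaving it out of the events raises the estimated curve.

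**4. Size, on assumed rates.** Let r be the yearly hazard of relapse, d the yearly hazard of death without relapse (both constant), and t the time in years.

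- Recurrence or death as event: S = exp(−(r + d)t)
- Relapse only, deaths censored at death: S = exp(−rt)

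With r = 0.025 and d = 0.005 to 0.010:

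| Years | Recurrence or death | Relapse only | Gap (points) |
|---|---|---|---|
| 2 | 94.2% to 93.2% | 95.1% | 0.9 to 1.9 |
| 5 | 86.1% to 83.9% | 88.2% | 2.2 to 4.3 |
| 10 | 74.1% to 70.5% | 77.9% | 3.8 to 7.4 |

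At 10 years: exp(−0.30) = 0.741, exp(−0.35) = 0.705 and exp(−0.25) = 0.779.

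**5. Sensitivity to the assumed rates.** Over r = 2-5% and d = 0.25-2% per year, with deaths censored at death, the 10-year gap runs from 1.5 points (r = 5%, d = 0.25%) to 14.8 points (r = 2%, d = 2%).

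**6. Events involved.** With r = 3% and d = 1% per year, and 790 patients followed completely for 10 years, there are about 790 × (1 − exp(−0.40)) = 260 events counting recurrence or death. Of these, 3/4, about 195, are relapses. About 65 deaths would drop out of the endpoint.

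**The case against.** **The contradiction may be only apparent.** The endpoint section never calls death an event. If death is meant there as true censoring, both sections make relapse the event. This cannot be ruled out from the wording alone, but it requires *censuring* to change meaning between adjacent sentences. Even so, the protocol would need correcting to say so. What stands is that the sponsor's intention is not known for certain, so the fix must allow for either.

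**Stronger readings that the protocol does not support**

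- *Dead patients stay at risk until the end of follow-up, adding immortal time.* A reader might infer this from the analysis section's wording. But that section does not define the end of follow-up, and the End of trial section ends participation at death, so censoring at death is an equally possible reading. The conflict over events remains either way.
- *An effect of exercise on death without relapse would be invisible.* It would be missing from recurrence-free survival only. All-cause survival is analysed at the same time points with the same methods.
- *The 4-7 points are a bias in the treatment comparison.* They are the distance between two endpoint definitions within one group of patients, on assumed hazards. They say nothing about a difference between arms.
- *Breast cancer-specific survival is analysed wrongly.* If patients are censored when they die of another cause, the planned Cox model is already a cause-specific model. Cumulative incidence in place of Kaplan-Meier is a method choice that a separate analysis plan may make.

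**Importance.** The endpoint is one part of one of nine secondary items, and the trial is not powered for it. Eligibility has no upper age limit, but it excludes conditions that prevent safe exercise, which may lower other-cause mortality. All of this stands and limits the severity.

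**Conclusion.** The point holds as a definition conflict. The endpoint section ends recurrence-free survival at recurrence or death; the analysis section counts breast cancer relapse only; nothing reconciles them. Following the analysis section leaves deaths without relapse out of the endpoint and gives a higher curve.

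The size depends on rates that the protocol does not give. The working figure of about 4-7 points at 10 years rests on constant hazards of 2.5% per year for relapse and 0.5-1.0% for other death, with deaths censored at death. The gap is small at 2 years and grows with follow-up. It is an overstatement only relative to the endpoint section's definition.

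This should be corrected before survival data are analysed. It does not threaten the trial's main conclusion.

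**What to change.** Use one definition in both sections: time from randomisation to the first recurrence (local, regional or distant) or death from any cause, whichever comes first, with patients censored at the last follow-up at which they were alive and relapse-free. Replace *censuring* by *event* wherever an event is meant, for all three survival endpoints.

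If relapse only is intended, give the endpoint a name that says so, and treat death without relapse as a competing event.

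For breast cancer-specific survival, state that follow-up ends at death from another cause. Cumulative incidence (Aalen-Johansen) in place of Kaplan-Meier is an optional addition.

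The cost is a change of wording. Recurrence and survival are already to be obtained from registers, and breast cancer-specific survival already requires cause of death, so no new data are needed. The sample size and primary analysis do not change.

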## Estimated sample size and power

Patients will be randomized in a 1:1 fashion. It is anticipated that the rate of the primary endpoint pCR will be approximately 30% in the control arm. We aim to increase the rate of pCR in the experimental arm to 40%, i.e. a 10 percentage points increase, which is regarded clinically relevant since it would translate into improved disease-related outcomes. With a power of 80% and an alpha of 5%, a total of 712 patients have to be included; 356 in each arm. Accounting for a drop-out of 10%, we aim to include 790 patients. Stratification at the moment of computerized randomization will be done based on site of treatment (hospital) and biological tumour subtype (ER+HER2-, ER+HER2+, ER-HER2+, ER-HER2-).

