#### Primary endpoint (pCR)

The primary outcome in this trial (pCR) is dichotomous, and will be assessed through histopathological examination of the surgical specimen after completed NACT. Hence, a multivariable logistic regression model, adjusting for biological tumour type (stratification factor in the randomization) will be used. The treatment effect will be assessed in terms of the resulting odds ratio between the two treatment arms together with a 95% confidence interval and a complementary Wald test. A two-sided statistical test with 5% significance level will be used. Furthermore, differences in pCR rates between the two treatment arms will be explored for each biological tumour type subgroup (ER+HER2-, ER+HER2+, ER-HER2+, ER-HER2-), using an interaction between treatment and biological tumour type.

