All health-related quality of life outcomes are measured as scores that range from 0 to 100, hence the outcomes are continuous. Both the global QoL score as well as the 17 subscales (8 scales reflecting symptoms and 9 reflecting function) will be assessed at four time points: baseline, pre-surgery, 1 and 2 years after surgery. To evaluate QoL scores at each time point both within and between the treatment groups, a mixed model for repeated measures (MMRM) will be used. Treatment, visit, treatment visit interaction and stratification factor biological tumour type will be included in the model as fixed effects, and patient as a random effect. An unstructured covariance matrix will be used to model the within-subject error. If the fit of the chosen structure fails to converge, the following covariance structures will be evaluated, in order, until convergence is reached: toeplitz with heterogeneity, autoregressive with heterogeneity, toeplitz, autoregressive and compound symmetry. Furthermore, differences in change from baseline between the treatment arms will be assessed at each time point by constructing relevant contrasts of the estimated regression coefficients.

1. *Self-reported physical activity*

Physical activity is reported using the Godin-Shephard Leisure-Time Physical Activity Questionnaire (GSLTPAQ) as total minutes per week of training in three intensity levels (light, moderate and intensive) and for weight training. Hence, the outcome is continuous. A mixed model for repeated measures (MMRM) will be used to assess physical activity at four different time points: baseline, pre-surgery, 1 and 2 years after surgery). The model will include treatment, visit, treatment-visit interaction and the stratification factor biological tumour type as fixed effects, and patient as a random effect. An unstructured covariance matrix will be used to model the within-subject error. If the fit of the chosen structure fails to converge, the following covariance structures will be evaluated, in order, until convergence is reached: toeplitz with heterogeneity, autoregressive with heterogeneity, toeplitz, autoregressive and compound symmetry. Physical exercise will be assessed both within and between the treatment groups. Furthermore, differences in change from baseline between the treatment arms will be evaluated at each time point by constructing relevant contrasts of the estimated regression coefficients.

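### The quality-of-life and self-reported-activity mixed models give each arm its own free baseline mean, so neither planned between-arm comparison is adjusted for the baseline value and precision is lost

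*Protocol*

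**What the plan says.** Under Secondary endpoints, the quality-of-life scores (a global score and 17 subscales) "will be assessed at four time points: baseline, pre-surgery, 1 and 2 years after surgery". The fixed effects of the repeated-measures model are written out: "Treatment, visit, treatment visit interaction and stratification factor biological tumour type will be included in the model as fixed effects". The covariance is unstructured.

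Two kinds of between-arm comparison are planned. One is of scores at each time point. The other is of change: "differences in change from baseline between the treatment arms will be assessed at each time point by constructing relevant contrasts of the estimated regression coefficients". Neither is ranked above the other.

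The self-reported physical activity model has the same visits, fixed effects, covariance and change contrasts. The general paragraph on covariate adjustment names tumour type and, where feasible, site. It does not mention the baseline value of the outcome.

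**The concern.** Treatment, visit and their interaction, with baseline among the visits, give each arm a separate baseline mean. The study calendar lists the baseline questionnaires above the randomisation row. If they are completed in that order, the arms share a baseline mean by design, and the model spends information estimating a difference whose true value is zero.

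The between-arm contrast at a visit then ignores the patient's starting value. The change contrast uses it only by subtraction, that is, with a fixed slope of 1. Either way the standard errors are larger than they need be. Quality of life and self-reported activity are named in the trial's second hypothesis and, under Reporting, secondary outcomes are tested at a Bonferroni-corrected level, so precision is scarce. The plan also yields two answers per post-baseline visit that can disagree because of chance imbalance alone.

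**Working it through.** **The plan's own figure.** The only power calculation is for pCR, under Estimated sample size and power. It takes about 30% for control against 40% for exercise, with equal allocation, and states: "With a power of 80% and an alpha of 5%, a total of 712 patients have to be included; 356 in each arm". The primary analysis is two-sided at 5%. With pooled variance under the null:

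n per arm = [1.960·√(2·0.35·0.65) + 0.842·√(0.30·0.70 + 0.40·0.60)]² / 0.10² ≈ 356, or 712 in total.

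The figure reproduces and is not affected by this point. No SD, effect size, correlation or power is given for quality of life or activity, so what follows rests on assumed values.

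**What the written model estimates.** With complete data, the change contrast equals the raw difference in mean change, because a tumour-type main effect cancels when visits are subtracted. This was checked on one simulated dataset of 300 patients with four visits and four tumour types. The three model change contrasts were −0.1848, −0.1202 and −0.2836 under two different covariance matrices, and the raw differences in mean change were identical. The visit contrasts did differ from raw means (for example 0.004 against −0.047 at the first post-baseline visit), because they are adjusted for tumour type.

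**Variance.** Let ρ be the correlation between baseline and follow-up, with equal SDs and complete data. In units of σ²/n per arm:

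- change contrast: 2(1−ρ)
- visit contrast: 1
- baseline-adjusted contrast: 1−ρ²

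Adjustment therefore leaves (1+ρ)/2 of the change-contrast variance and 1−ρ² of the visit-contrast variance. If the planned contrast has 80% power at two-sided 5%, the adjusted contrast has power Φ(2.802/√ratio − 1.960). For ρ = 0.5: 2.802/√0.75 = 3.235, and Φ(1.275) = 89.9%.

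| ρ (assumed) | Ratio, change | Ratio, visit | Adjusted power, from 80% for change | Adjusted power, from 80% for visit |
| --- | --- | --- | --- | --- |
| 0.3 | 0.65 | 0.91 | 93.5% | 83.6% |
| 0.5 | 0.75 | 0.75 | 89.9% | 89.9% |
| 0.7 | 0.85 | 0.51 | 86.0% | 97.5% |

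In effective numbers, 712 patients carry the information of 463, 534 and 605 under the change contrast (712 × ratio), and of 648, 534 and 363 under the visit contrast. The better planned contrast is the visit mean at ρ = 0.3, either at 0.5, and change at 0.7. Against it the gain is about 4, 10 and 6 points.

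**Imbalance.** Given a chance baseline difference d, the visit contrast is shifted by ρd and the change contrast by −(1−ρ)d. At ρ = 0.5 and d = 0.1 SD these are +0.05 and −0.05 SD.

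**Unequal SDs.** With k = baseline SD / follow-up SD, the ratio for change is (1−ρ²)/(1+k²−2ρk). From 80%:

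- ρ = 0.5, k = 0.8: 0.75/0.84 = 0.893, power about 84%
- ρ = 0.7, k = 0.9: 0.51/0.55 = 0.927, power about 83%
- ρ = 0.7, k = 0.8: 0.51/0.52 = 0.981, power about 81%

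The visit ratio does not depend on k.

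**Incomplete follow-up, ρ = 0.5.** The variance of either planned contrast relative to the adjusted one is 1.33 with complete data and 1.30 if 10% of patients have baseline only. If half lack the one- and two-year visits (an assumption), it is 1.18 at those visits, so 80% becomes about 86% there.

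**The case against.** The strongest reply is that nothing here is invalid. A reader might infer bias or an inflated error rate. The documents do not support that: under randomisation both planned contrasts are unbiased and each test keeps its type I error. These are secondary endpoints for which no power is claimed, and the primary analysis is untouched. All of this stands and sets the weight of the point.

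Other strong readings also fail:

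- *The visit comparisons are raw differences in means.* Tumour type is in the model, so they are unadjusted for baseline only.
- *The baseline measurement is discarded.* The change contrast uses it by subtraction, and with incomplete follow-up the likelihood borrows from it.
- *The gain over the change contrast is always more than 5 points.* That needs equal SDs, which an unstructured covariance does not assume. Equality is doubtful for activity, because the exclusion of people already meeting the exercise threshold may narrow the baseline spread.
- *The follow-up data are complete.* The study calendar marks the one- and two-year EORTC and Godin questionnaires with the asterisk that restricts items to Stockholm sites. If that holds, the gain at those visits shrinks.

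Finally, the calendar labels the baseline row by the start of chemotherapy. That it precedes randomisation is read from row order. The order supports a common baseline mean, but for self-reports in an unblinded trial the timing should be confirmed. If knowing the allocation affected the baseline answers, the planned change contrast would be distorted too.

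**Conclusion.** The point holds as one of precision and of sensitivity to chance baseline imbalance, on secondary endpoints. It is not about bias or type I error. The model terms and contrasts are written out in the protocol, so this is a stated choice and not a detail left open.

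The gain over the better planned contrast is about 4 to 10 power points from a hypothetical 80%. That assumes complete data, equal SDs, ρ between 0.3 and 0.7 and an unadjusted two-sided 5% level. It can fall to about 1 point (ρ = 0.7, baseline SD 0.8 of follow-up SD). Over the weaker planned contrast it is larger, and the plan does not say which contrast will carry the conclusion. Because the improvement uses data already collected, it should be made.

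**What to change.** In the quality-of-life and self-reported-activity paragraphs, do one of the following:

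1. Keep baseline in the response vector and fit visit plus treatment-by-post-baseline-visit terms with no treatment main effect, so that the arms share one baseline mean. State that the baseline questionnaires are completed before randomisation.
2. Use the post-baseline visits as the response, with baseline score and baseline-by-visit as covariates.

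The two are close but not identical. Tumour type and the covariance sequence stay as planned. Name the baseline-adjusted difference at each post-baseline visit as the between-arm comparison, in place of the two now planned. Under option 1, within-arm changes remain available from the same fit.

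The cost is a wording change. Data, visits, software procedure and the pCR sample size are unaffected.
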